### Secondary Outcome Measure

Based on OSBIE data from 1999-2002, we estimate a baseline injury rate of 15 reported injuries per 1000 student years. Anticipating a 33% reduction in injuries overall, and using the method above, we estimate that 15 clusters per arm or 30 schools in total will be required. 37 schools have been randomized so the study should have ample power, and would potentially be able to detect smaller differences.

Severe head injuries are rare events. They will be recorded because of their importance but we do not anticipate a statistically significant difference because of the small numbers.

## What is the planned recruitment rate?

All schools will be recruited at the beginning of the trial and we anticipate that all schools will agree to participate. Our previous work with OSBIE data suggests 15 playground injuries per 1000 students per year. Approximately 225 playground injuries per year will occur among 15,000 students, or 23 per month across the ten months school is in session. We believe that 90% of parents of injured children will agree to participate as there is only a minor inconvenience (one phone call) associated with participation and we have achieved this rate of participation in a previous telephone survey of play equipment injuries in Toronto (26).

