## What are the proposed primary and secondary outcome measures?

### Primary Outcome Measure - Upper Extremity Fracture Rates

The primary outcome is an upper extremity fracture occurring on the school playground. The definition of an upper extremity fracture will be parental report of a physician’s diagnosis of ‘break’, ‘fracture’, or ‘dislocation’ in children who were x-rayed AND required a cast, splint or sling.

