## How will the outcome measures be measured at follow-up?

Ontario School Board Insurance Exchange (OSBIE) incident reports are routinely completed by teachers for any injury (playground or other) in every TDSB school. The threshold for completing an OSBIE form is ‘when someone receives medical/dental attention’. Inservices will be held for teachers at each school to remind them of the forms and the threshold for completion, as a means of standardizing the reporting.

The research assistant will receive new OSBIE incident reports describing playground injuries at each school on a weekly basis.

Parents of children who are injured will be contacted by telephone (after initial contact by letter) for consent and data collection. The CHIRPP form (see appendix) will be completed by telephone, such use has been validated (24). Additional telephone questions added to the CHIRPP form for details on the event and the injury are given in the appendix. The research assistant will work flexible hours allowing evening phone calls to parents where necessary. Hospital for Sick Children language line interpreter services will be used if a parent or caregiver has insufficient English.

To validate the injury data for severe injuries, health records (emergency sheet, and discharge sheet if admitted) will be obtained (with consent) for all children attending an emergency department or admitted to a hospital. ICD 10 diagnostic and procedure codes will be abstracted from emergency and inpatient records by trained coders.

We expect that the OSBIE incident reports will capture all severe injuries especially if there is an absence from school. A small number of injuries may have a delayed presentation (after school hours), and not be reported via the OSBIE incident reports. We expect that the school (ie the principals) would be notified if the injury was severe. Principals will be contacted monthly to ensure that no playground injuries have been missed

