## What is the likely rate of loss to follow-up?

We expect minimal loss to follow up because parents of injured children are only required to complete one telephone interview. The research assistant will manage requesting and receiving medical records once consent is obtained.

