## Give details of the planned analyses

### Primary outcome:

The primary analysis will include all randomized schools and upper extremity fractures as defined in Section 2.8.1. This effectiveness analysis will compare the rates of injuries in the two groups. A poisson model will be used since the outcomes are counts. For each school we will observe X, the number of injuries reported over the two-year period, and Y, the student-years accumulated over the two-year period. The estimated injury rate for each school is X/Y, with estimated variance X/Y2. Using methods proposed by Thompson et al. (27), an overall injury rate for each type of school (Fibar® or granite sand), along with the corresponding variances will be estimated. This method accounts for the extra variation due to the clustering. The injury rates can then be compared by a Z-statistic which is the difference in the two rates divided by the square root of the sum of the corresponding variances. Covariate adjustment for school level variables such as average age, proportion of males, school size, socioeconomic status, and surface depth will be facilitated using methods given by Raudenbush (28).

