### Data Collection, Handling, Computerization and Analysis

Faxed copies of OSBIE incident reports will be sent from the school to the research assistant at the Hospital for Sick Children. The research assistant will then contact parents by letter to inform them of the study and then by telephone (evening where necessary) to obtain verbal consent to participate in the study. The CHIRPP form and appendix will be used to collect specific information regarding the injury. HSC telephone interpreter services will be used where necessary if English is not the first language. Faxed copies of emergency room or inpatient discharge sheets will be sent to the research assistant at HSC and will be coded using ICD 10 codes for diagnosis and procedures. A secure trial database will be maintained at The Hospital for Sick Children using ACCESS software. Completed data will be exported from ACCESS for analysis in SAS-PC.

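### Fractures in children whose parents do not take part drop out of the numerator but stay in the student-years, so both arm rates and their difference run about 10% low, and the sample size makes no allowance for it

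*Protocol*

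**What the plan says.** Protocol, Primary Outcome Measure: "The definition of an upper extremity fracture will be parental report of a physician". The sentence continues with the diagnoses that qualify (break, fracture or dislocation) and restricts the outcome to injuries "in children who were x-rayed AND required a cast, splint or sling".

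Protocol, How will the outcome measures be measured at follow-up: "Parents of children who are injured will be contacted by telephone (after initial contact by letter) for consent and data collection". The same section makes access to emergency and discharge records, used to validate severe injuries, conditional on consent. Ethical Issues repeats that consent is voluntary and is taken by telephone.

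Protocol, What is the planned recruitment rate: "We believe that 90% of parents of injured children will agree to participate as there is only a minor inconvenience".

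Protocol, Details of the planned analyses, Primary outcome: for each school the analysis takes X, the count, and "Y, the student-years accumulated over the two-year period". The rate is X/Y with variance X/Y², and the arms are compared by a Z-statistic on the rate difference. The sample size section arrives at its student-years from all enrolled pupils.

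Protocol, Data Collection: "Faxed copies of OSBIE incident reports will be sent from the school to the research assistant". This happens before parents are approached.

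**The concern.** Numerator and denominator do not cover the same children. A fracture can enter X only if a parent consents and is interviewed, whereas Y includes every pupil. Nothing in the protocol classifies a fracture by another route when the parent declines or is not reached, reduces Y to match, or treats such a report as missing. Incident reports and the monthly contact with principals find injuries, but they do not supply the parent-reported diagnosis, x-ray and immobilization that the definition requires.

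Three things are at stake:
- The absolute fracture rates and the rate difference that the Z-statistic tests.
- The injury probabilities in the economic model that rest on classified outcomes, since that model takes its probabilities from the observed rates.
- The margin of power claimed in the sample size section.

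Head injury and the reanalysis of displaced fractures share the problem. Overall playground injury does not, because an incident report alone is enough for it.

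**Working it through.** **Inputs from the protocol.** Rates λ0 = 0.004 and λ1 = 0.002 per student-year; y = 820 student-years per school; k = 0.2, with ample power claimed for k from 0.1 to 0.3; alpha 0.05; power 80%; 19 wood fibre and 18 sand schools; participation p = 0.90. **Assumptions made here.** The test is two-sided (this reproduces the stated figure); p applies equally to fracture cases and to both arms; wood fibre carries the higher rate.

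**1. The plan's own figure.** The Hayes method for unmatched clusters is

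c = 1 + (1.960 + 0.842)² × [(λ0 + λ1)/y + k²(λ0² + λ1²)] / (λ0 − λ1)²

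- (0.006)/820 = 7.317×10⁻⁶
- 0.04 × (1.6×10⁻⁵ + 0.4×10⁻⁵) = 0.800×10⁻⁶
- c = 1 + 7.849 × 8.117×10⁻⁶ / 4×10⁻⁶ = 16.93, so 17 per arm and 34 schools, as stated.

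The calculation uses the full rates and so assumes that every fracture is ascertained.

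**2. Rates and counts at 90%.**
- 0.9 × 4.0 = 3.6 and 0.9 × 2.0 = 1.8 per 1000. The difference is 1.8 instead of 2.0, and the ratio stays at 0.50.
- Expected fractures: 19 × 820 × 0.004 + 18 × 820 × 0.002 = 62.3 + 29.5 = 91.8.
- Countable: 56.1 + 26.6 = 82.7. About 9 are lost.

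**3. Schools needed at 90%, y unchanged.**
- (0.0054)/820 = 6.585×10⁻⁶
- 0.04 × (0.0036² + 0.0018²) = 0.648×10⁻⁶
- c = 1 + 7.849 × 7.233×10⁻⁶ / 3.24×10⁻⁶ = 18.52, so 19 per arm and 38 schools against 37 randomized.

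**4. Power with 19 and 18 schools.** Variance of the difference: V = (λ0/y + k²λ0²)/18 + (λ1/y + k²λ1²)/17. Power = Φ(|λ0 − λ1|/√V − 1.96).

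- k = 0.2, full ascertainment: 0.0020/0.000678 = 2.95, power 83.9%.
- k = 0.2, 90%: 0.0018/0.000640 = 2.81, power 80.3%.

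| k | Schools per arm, full | Power, full | Schools per arm, 90% | Power, 90% |
|---|---|---|---|---|
| 0.1 | 16 | 86.5% | 18 | 82.9% |
| 0.2 | 17 | 83.9% | 19 | 80.3% |
| 0.3 | 19 | 79.5% | 21 | 76.1% |

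The standard error shrinks along with the difference, so the loss of power is smaller than the 10% loss in the estimate might suggest.

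**5. Unequal participation.** The observed sand to wood fibre ratio is the true ratio multiplied by (participation in sand schools)/(participation in wood fibre schools). It is unbiased when the two are equal. The document gives no participation figure by arm.

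**The case against.** The strongest case on the other side is that no sentence tells the analyst to score an unclassified report as zero, and that missing-outcome handling usually belongs in an analysis plan, which is not shown. The choice of method can indeed wait for that plan. The mismatch cannot, because it comes from the outcome definition, the consent route and the estimator, all of which the protocol fixes. An analysis plan would have to depart from the definition to count these fractures.

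It is also fair that the effect is modest. With equal participation the ratio and the null hypothesis are preserved, there is no false-positive bias, and power at k = 0.2 stays at its target. The 90% refers to parents of all injured children, and participation could be higher or lower where there is a fracture. The economic section varies outcome probabilities in sensitivity analysis, which can examine a 10% shortfall but leaves the base case low.

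Two stronger readings are tempting and are not supported:
- A reader might infer that the comparison between surfaces is biased because the surface is visible and schools know the trial's purpose. The letter, call, interpreter service and consent process are the same in both arms, and nothing indicates that willingness to take the call depends on surface. The protocol's remark that parent report should not differ by surface concerns accuracy, not participation, so the possibility is neither shown nor excluded.
- A reader might infer that the loss-to-follow-up section is wrong: "We expect minimal loss to follow up because parents of injured children are only required to complete one telephone interview". Refusing consent and being lost after consenting are different quantities, and the protocol discloses the first elsewhere. The two statements need not contradict each other.

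**Conclusion.** The point holds in a limited form and should be corrected. As written, both arm rates and the tested rate difference are understated by about 10% at the protocol's own participation figure. This assumes that 90% also applies to fracture cases and, for the count of about 9 lost of 92, that the planning rates are true. The rate ratio is distorted only if participation differs by arm.

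The claim of ample power for k between 0.1 and 0.3 does not survive as stated. At 90% ascertainment power is 82.9%, 80.3% and 76.1% at k = 0.1, 0.2 and 0.3. At k = 0.3 it is just under 80% (79.5%) even with full ascertainment. The appendix cited for that range was not available, so this rests on the formula in the main text.

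**What to change.** 1. Code body part and suspected injury from the incident report for every injured child. This is subject to ethics confirmation that these fields may be used without an interview, and to what the form records. The form is not shown to hold the x-ray and cast, splint or sling items, so full classification from it cannot be assumed.
2. Correct the arm rates for unclassified arm-injury reports, by weighting by 1/participation within arm and body part or by multiple imputation. State the assumption that participation is unrelated to fracture status given arm and body part.
3. If weights are used, replace the variance X/Y² by the sum of squared weights over Y². Putting the weighted count into X/Y² would understate the within-school variance by the factor p, here 0.9.
4. Present alongside it the participants-only analysis and simple bounds, with all unclassified arm injuries counted as fractures and then as none.
5. Report participation by arm, and use the corrected rates in the economic base case.
6. Restate the power claim with the ascertainment allowance. Weighting restores the level of the rates but not the lost information.

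The cost is small. At 225 injuries a year over two years there are about 450 reports to code, of which about 45 (10%) would lack an interview. The drawbacks are some extra analysis and a missing-at-random assumption that the trial cannot test. The coding should be arranged before data collection, because fields not captured for non-participants may not be recoverable later.

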## Are there likely to be any problems with compliance?

We do not anticipate problems with compliance because no ongoing actions are required by the schools after the playground surfaces are installed. Actual treatment installed will be recorded three times per year during site visits.

## What is the likely rate of loss to follow-up?

We expect minimal loss to follow up because parents of injured children are only required to complete one telephone interview. The research assistant will manage requesting and receiving medical records once consent is obtained.

## Give details of the planned analyses

### Primary outcome:

The primary analysis will include all randomized schools and upper extremity fractures as defined in Section 2.8.1. This effectiveness analysis will compare the rates of injuries in the two groups. A poisson model will be used since the outcomes are counts. For each school we will observe X, the number of injuries reported over the two-year period, and Y, the student-years accumulated over the two-year period. The estimated injury rate for each school is X/Y, with estimated variance X/Y2. Using methods proposed by Thompson et al. (27), an overall injury rate for each type of school (Fibar® or granite sand), along with the corresponding variances will be estimated. This method accounts for the extra variation due to the clustering. The injury rates can then be compared by a Z-statistic which is the difference in the two rates divided by the square root of the sum of the corresponding variances. Covariate adjustment for school level variables such as average age, proportion of males, school size, socioeconomic status, and surface depth will be facilitated using methods given by Raudenbush (28).

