## Why is a trial needed now?

Despite the importance of playground injuries, to date, there are no randomized trials of injury countermeasures. Published intervention studies are pre post studies without injury outcomes. Therefore, they cannot be used to guide decision making. By examining injury rates by type of surface, it may be possible to dramatically reduce the numbers and severity of children’s playground injuries. Last, there is a unique opportunity to perform this study within an existing program of playground replacement carried out by the Toronto District School Board. This means that a high quality randomized trial can be conducted with high leverage and modest cost. In the summer of 2000, the Toronto District School Board (TDSB) removed playground equipment that did not comply with newly revised Canadian Standards Association (CSA) standards (20). Subsequently, there has been a phased replacement of equipment. In the spring of 2003, retrofitting and replacement of equipment began in 37 school playgrounds that had partial equipment removal. Both wood (Fibar®) and granite sand surfaces are routinely used in TDSB schools. The Toronto District School Board agreed to randomize surfacing for these 37 schools, allowing an ideal opportunity to determine the relationship between surface type and playground injury rates. The $1.7M cost of replacing the playgrounds according to the randomization schedule was covered by the TDSB. Playground injuries can be identified from a prospectively recorded population based database (Ontario School Board Insurance Exchange - OSBIE). The playgrounds have a service life of 10 to 20 years, so outcomes from this randomized cohort can be assessed once funding is secured.

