## What is the allocation method?

A computer generated random number list was used to assign the 37 participating schools to Fibar® or granite sand groups. School level covariates including student population, socioeconomic status, and playground size are balanced between the groups as shown in table 1 below:

Table 1: Results of Randomization:

|  | **Fibar Schools**  **N = 19**  **Mean (S.D.)** | **Granitic Sand Schools**  **N = 18**  **Mean (S.D.)** | **P-Value** |
| --- | --- | --- | --- |
| Number of Students | 409.2 (312.1) | 416.3 (195.4) | 0.934 |
| Learning Opportunities Index (LOI) | 0.55 (0.27) | 0.49 (0.29) | 0.533 |
| Size of Playground (m2) | 18826.6 (22657.1) | 17142.8(22589.3) | 0.835 |
| TDSB Budget ($) | 42914.6 (31086.8) | 48658.70 (27426.2) | 0.555 |
| Cost of re-surfacing ($) | 7073.68 (1442.55) | 5688.9 (1179.9) | 0.003 |

Note: The TDSB Learning Opportunities Index 2002-03 combines information from the following variables: average and median income of families with school-aged children; parental education; proportion of lone-parent families; recent immigration; housing type (apartment, single detached housing); student mobility. It is the standard socioeconomic status measure for TDSB schools.

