### Primary Outcome Measure

Based on OSBIE data from 1999-2001 we estimate a baseline arm fracture (lambda zero) rate of 4 per 1000 student years. A clinically significant difference would be a halving of this rate to 2 per 1000 student years (lambda one). This is consistent with reports of sand having ½ to 1/6 the injury rate of other surfaces (14). Each school of 410 students provides 820 student years (y) of data over the two year study. Hayes’ method of sample size estimation for cluster randomization was used (25), where the number of clusters (c) per arm is:

Setting alpha = .05 and power at 80%,and k (coefficient of variation between clusters) at 0.2, we estimate that 17 clusters per arm or 34 schools in total will be required. 37 have been randomized so the study should have ample power. Ample power exists if the coefficient of variation is between 0.1 and 0.3 (see appendix).

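### Each school's pre-installation OSBIE report rate is neither obtained nor used, which gives up some precision and a check on chance imbalance in risk and reporting habit

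*Protocol*

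**What the plan says.** The protocol's section on planned analyses (Primary outcome) names the adjustment variables: "Covariate adjustment for school level variables such as average age, proportion of males, school size, socioeconomic status, and surface depth will be facilitated". The sections on co-interventions and covariates add falling heights and a supervision ratio. The section on the allocation method claims: "School level covariates including student population, socioeconomic status, and playground size are balanced between the groups". Its Table 1 compares student numbers, the Learning Opportunities Index, playground size, budget and resurfacing cost. Outcomes are collected for two school years after installation only.

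The same protocol already draws on earlier OSBIE records. In the sample-size section: "Based on OSBIE data from 1999-2001 we estimate a baseline arm fracture (lambda zero) rate of 4 per 1000 student years" and "Based on OSBIE data from 1999-2002, we estimate a baseline injury rate of 15 reported injuries per 1000 student years". The section on why a trial is needed now says of OSBIE: "Playground injuries can be identified from a prospectively recorded population based database". The section on how outcomes are measured describes the reports as routine in every board school. No section uses a school's earlier report rate for allocation, for the balance check or for adjustment.

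**The concern.** Case finding rests mainly on a teacher filing an incident report. A school's earlier report rate reflects both its underlying playground risk and its readiness to report. None of the listed covariates measures readiness to report. With 19 and 18 schools, and a random list with no stratification or matching described, the arms can differ by chance on both, and Table 1 cannot show it.

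A rate fixed before allocation can be adjusted for without risk of bias, and it removes part of the between-school variance. This is more than a covariate choice that could wait for an analysis plan, because an analysis plan can only adjust for data that someone has collected, and the protocol provides for no such extract.

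**Working it through.** **Inputs from the protocol's sample-size section.** Fracture rates 4 and 2 per 1000 student-years. All injuries 15 per 1000 with a 33% reduction, taken as 15 and 10. y = 820 student-years per school (410 students, two years). Also: "Setting alpha = .05 and power at 80%,and k (coefficient of variation between clusters) at 0.2, we estimate that 17 clusters per arm". The protocol calls power ample for k from 0.1 to 0.3. Two-sided testing is assumed, because sidedness is not stated.

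**Step 1: reproduce the plan.** Hayes-Bennett formula for unmatched rates:

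c = 1 + (1.960 + 0.842)² × [(λ0 + λ1)/y + k²(λ0² + λ1²)] / (λ0 − λ1)², where the squared sum of normal quantiles is 7.849.

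- Fractures, k = 0.2: 0.006/820 = 7.317e-6 and 0.04 × 2.0e-5 = 0.800e-6, total 8.117e-6. c = 1 + 7.849 × 8.117e-6 / 4e-6 = 16.93, so 17, as stated.
- All injuries, k = 0.2: 0.025/820 = 3.049e-5 and 0.04 × 3.25e-4 = 1.300e-5, total 4.349e-5. c = 1 + 7.849 × 4.349e-5 / 2.5e-5 = 14.65, so 15, as stated.
- At k = 0.3 the same formula gives 18.89 (19 per arm, 38 schools) for fractures and 19.75 (20 per arm) for all injuries, against 37 schools randomised.

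**Step 2: how much variance a baseline could remove.** The between-school share of the variance for fractures is 0.800/8.117 = 9.9% at k = 0.2 and 19.7% at k = 0.3. For all injuries it is 30% and 49%. Only this share can be reduced.

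**Step 3: size of chance imbalance.** The standard error of the log ratio of underlying rates is k × √(1/19 + 1/18) = 0.329k. The 95% range of the ratio is 0.88 to 1.14 at k = 0.2 and 0.82 to 1.21 at k = 0.3.

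**Step 4: adjust for the all-injury baseline.** Assume that the school effect is stable and is shared by fractures and all injuries. Three baseline years give m = 0.015 × 410 × 3 = 18.45 expected reports per school; one year gives 6.15. The share of between-school variance explained is R = k²/(k² + 1/m), and the remaining coefficient of variation is k√(1 − R).

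- k = 0.2, three years: R = 0.0400/(0.0400 + 0.0542) = 0.425, remaining k = 0.152.
- k = 0.3, three years: R = 0.0900/(0.0900 + 0.0542) = 0.624, remaining k = 0.184.

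Power with c = 18 per arm is Φ{√[(c − 1)(λ0 − λ1)²/V] − 1.960}, where V is the bracketed variance in Step 1. Fractures at k = 0.2, unadjusted: √(17 × 4e-6 / 8.117e-6) = 2.894, and Φ(0.934) = 82.5%. Adjusted: V = 7.777e-6, √8.743 = 2.957, and Φ(0.997) = 84.1%.

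| Outcome | k | Unadjusted | One baseline year | Three baseline years |
|---|---|---|---|---|
| Fractures | 0.2 | 82.5% | 83.2% | 84.1% |
| Fractures | 0.3 | 78.0% | 80.9% | 83.1% |
| All injuries | 0.2 | 87.8% | 89.7% | 91.7% |
| All injuries | 0.3 | 76.0% | 83.5% | 89.3% |

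With three years, the schools needed per arm stay at 17 for fractures at k = 0.2 (16.26). At k = 0.3 they fall from 19 to 17 for fractures and from 20 to 15 for all injuries. A fracture-only baseline (0.004 × 410 × 3 = 4.92 events per school) is weaker: at k = 0.2, power for fractures goes from 82.5% to 83.1%.

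**The case against.** A reader might infer that the primary comparison is biased, or that the protocol's statement of balance is false. Neither follows. Chance differences between schools are already carried in k in the sample size, and the planned analysis uses a variance that allows for clustering. They widen the interval and do not bias the test. The balance statement covers named variables only, and Table 1 shows them.

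A reader might also infer that every outcome depends on a teacher's decision to report. The protocol adds monthly contact with principals as a second route. It also has a common form and written policy, in-service sessions, and an expectation that fractures are reported consistently because they are severe.

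Further points stand:

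- At the plan's own k of 0.2 the gain for the primary outcome is under two points of power.
- The wording of the covariate list is open, so a prior rate is not excluded. It is simply neither named nor collected.
- Past and future rates may be only loosely linked. Equipment was partly removed in 2000 and later replaced, and the in-service sessions aim to make reporting more uniform.
- The trial's fracture definition needs a parent interview, which past reports lack. The all-injury report rate is therefore the usable baseline.
- The planning rates are aggregates. Retrieval by school for these 37 schools is implied, not stated.

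These points limit the size of the gain. They do not remove the omission, and the remedy is cheap.

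**Conclusion.** The omission is real and worth correcting, but it is a missed gain, not an error or a contradiction. The unadjusted randomised analysis remains valid. For fractures the benefit is small at k = 0.2 (at most 1.6 points of power) and moderate at k = 0.3 (at most 5.1 points). For all injuries it is at most 3.9 and 13.3 points. At k = 0.3, inside the range the protocol calls ample, the unadjusted formula needs slightly more schools than were randomised for fractures, and an effective baseline would bring that back within 37.

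These are upper bounds. They rest on three baseline years, equal schools of 410 students, a school effect that is stable over time, and fractures sharing the all-injury effect. With one baseline year the gain is roughly halved at k = 0.2. It shrinks further if the 2000 equipment removal or the in-service sessions weaken the link, and for fractures it vanishes if they do not share the school effect. Separately from precision, a table of past rates by arm would give direct evidence on balance in risk and reporting, which Table 1 lacks.

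**What to change.** First confirm that OSBIE playground reports can be retrieved by school. If so:

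- Extract reports and student-years for the 37 schools for the years before the spring 2003 allocation, with periods before and after the summer 2000 equipment removal shown separately.
- Add the report rate by arm to Table 1.
- In the Primary outcome and Secondary outcome analysis sections, prespecify the rate as a school-level baseline covariate in the adjusted analyses of fractures and of all injuries. Use a form that tolerates schools with no reports, such as a shrunken or continuity-corrected log rate. The unadjusted comparison stays as planned.
- Take surface depth out of the main adjusted model. It is measured after installation, and the co-interventions section allows that maintenance may differ systematically between groups. A rate fixed before allocation cannot be affected by the surface.

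The cost is one data extract and one model term, with no added visits or participants. Outcome collection is described as still awaiting funding, so the covariate can be fixed before any outcome is seen.
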